## **F. Social Skills Improvement System (SSIS) Rating Scales, Parent version, (1998)**

Het is de bedoeling dat u bij onderstaande beschrijvingen (middels nooit, soms, vaak) aangeeft in welke mate deze van toepassing is op uw kind zoals hij/zij nu is of in de afgelopen twee weken is geweest.

|                                                                                              | Nooit          | Soms           | Vaak           |
|----------------------------------------------------------------------------------------------|-----------------------|-----------------------|-----------------------|
| 1. Gaat thuis op een goede manier met vrije tijd om.                                         |  |  |  |
| 2. Houdt uit zichzelf zijn/haar kamer schoon en netjes.                                      |  |  |  |
| 3. Spreekt thuis met een normaal stemgeluid.                                                 |  |  |  |
| 4. Neemt uit zichzelf deel aan groepsactiviteiten.                                           |  |  |  |
| 5. Stelt zich voor aan onbekende mensen, zonder hiertoe aangezet te hoeven worden            |  |  |  |
| 6. Reageert op een goede manier wanneer andere kinderen hem/haar duwen of slaan              |  |  |  |
| 7. Vraagt winkelpersoneel om informatie of hulp.                                             |  |  |  |
| 8. Luistert wanneer een volwassene een groep toespreekt.                                     |  |  |  |
| 9. Weigert beleefd onredelijke verzoeken van anderen.                                        |  |  |  |
| 10. Nodigt anderen thuis uit.                                                                |  |  |  |
| 11. Feliciteert gezinsleden met prestaties.                                                  |  |  |  |
| 12. Maakt gemakkelijk vrienden.                                                              |  |  |  |
| 13. Heeft veel interesses.                                                                   |  |  |  |
| 14. Vermijdt situaties die problemen zouden kunnen geven.                                    |  |  |  |
| 15. Ruimt speelgoed of andere spullen in het huis op.                                        |  |  |  |
| 16. Biedt uit zichzelf hulp aan bij taken.                                                   |  |  |  |
| 17. Reageert goed op kritiek.                                                                |  |  |  |
| 18. Neemt op een goede manier de telefoon aan.                                               |  |  |  |
| 19. Helpt uit zichzelf met huishoudelijke taken.                                             |  |  |  |
| 20. Stelt op een goede manier huisregels die onrechtvaardig zouden kunnen zijn ter discussie |  |  |  |
| 21. Probeert huishoudelijke taken zelf uit te voeren, voordat hij/zij om hulp vraagt         |  |  |  |
| 22. Beheerst woede bij ruzie met andere kinderen.                                            |  |  |  |
| 23. Wordt aardig gevonden door andere kinderen                                               |  |  |  |
| 24. Begint eerder zelf een gesprek dan te wachten tot anderen daarmee beginnen               |  |  |  |

|                                                                                                     | Nooit          | Soms           | Vaak           |
|-----------------------------------------------------------------------------------------------------|-----------------------|-----------------------|-----------------------|
| 25. Beëindigt onenigheid met u op een rustige manier.                                               |  |  |  |
| 26. Beheerst woede in conflictsituaties met u.                                                      |  |  |  |
| 27. Geeft complimentjes aan vriendjes of andere kinderen in het gezin.                              |  |  |  |
| 28. Voert binnen een redelijke tijd huishoudelijke taken uit.                                       |  |  |  |
| 29. Vraagt toestemming om spullen van gezinsleden te gebruiken.                                     |  |  |  |
| 30. Heeft zelfvertrouwen in sociale situaties, zoals feestjes of groepsuitjes.                      |  |  |  |
| 31. Vraagt toestemming om naar buiten te gaan.                                                      |  |  |  |
| 32. Reageert op een goede manier op pesten van vriendjes, broertjes of zusjes.                      |  |  |  |
| 33. Maakt goed gebruik van de tijd dat hij/zij moet wachten op uw hulp bij huiswerk of andere taken |  |  |  |
| 34. Accepteert voorstellen van vriendjes om samen dingen te gaan doen.                              |  |  |  |
| 35. Maakt gemakkelijk de overgang van de ene activiteit naar de andere.                             |  |  |  |
| 36. Werkt uit zichzelf samen met gezinsleden.                                                       |  |  |  |
| 37. Reageert goed op complimenten van vriendjes.                                                    |  |  |  |
| 38. Meldt ongelukken bij de aangewezen personen.                                                    |  |  |  |

### **G. BRIEF Parent Version, Subscale Working Memory, version 01**

Het is de bedoeling dat u bij onderstaande beschrijvingen (middels nooit, soms, vaak) aangeeft in welke mate deze van toepassing is op uw kind zoals hij/zij nu is of in de afgelopen twee weken is geweest.

|                                                                                     | Nooit                 | Soms                  | Vaak                  |
|-------------------------------------------------------------------------------------|-----------------------|-----------------------|-----------------------|
| 1. Onthoudt alleen het eerste of het laatste als hij/zij drie dingen te doen krijgt |  |  |  |
| 2. Kan zich maar kort concentreren                                                  |  |  |  |
| 3. Heeft moeite zich te concentreren op karweitjes, schoolwerk etc.                 |  |  |  |
| 4. Is snel afgeleid door geluid, activiteit, uitzicht etc.                          |  |  |  |
| 5. Heeft moeite met karweitjes of taken die meer dan een stap vereisen              |  |  |  |
| 6. Heeft hulp nodig van een volwassene om bij de les te blijven                     |  |  |  |
| 7. Vergeet wat hij/zij aan het doen was                                             |  |  |  |
| 8. Als hij/zij iets moet halen, vergeet hij/zij wat het ook alweer was              |  |  |  |
| 9. Heeft moeite om dingen af te maken (karweitjes, huiswerk)                        |  |  |  |
| 10. Heeft moeite om dingen te onthouden, zelfs voor een paar minuten                |                       |                       |                       |

## H. Self Efficacy children, Self constructed questionnaire, version 02

### Hoe ik over mijzelf denk.

Maak eerst de oefenvraag, zodat je weet hoe je straks de echte vragen moet beantwoorden.

#### Oefenvraag

Als nu aan je gevraagd werd om dingen op te tillen die een verschillend gewicht hebben, hoe zeker ben je dat je de volgende gewichten kan optillen:

Geef aan hoe zeker je bent door het aanduiden van een getal tussen de 0 en de 10, zoals aangegeven op onderstaande schaal.

[figure not shown]

Optillen van een pak suiker

[figure not shown]

Een ingepakte koffer

[figure not shown]

Een tafel

[figure not shown]

Een auto

[figure not shown]

### Vragenlijst voor kinderen

Deze vragenlijst is gemaakt, zodat wij beter begrijpen welke soort dingen kinderen moeilijk vinden om te doen.

Geef bij de volgende dingen aan hoe zeker je bent dat je deze dingen kan doen. Dit doe je door een nummer van 0-10 aan te duiden vullen.

1. Ik ben er zeker van dat ik naar een uitleg kan luisteren als ik haast heb.

[figure not shown]

2. Ik ben er zeker van dat ik mijn taken kan plannen binnen een bepaalde tijd.

[figure not shown]

3. Ik ben er zeker van dat ik een vriend(in) of klasgenoot kan helpen, ook al heb ik zelf dingen die ik moet doen.

[figure not shown]

4. Ik ben er zeker van dat ik de tijd in de gaten kan houden door op een klok of horloge te kijken, zodat ik mijn taken op tijd af krijg.

[figure not shown]

5. Ik ben er zeker van dat ik naar een uitleg kan luisteren, zonder er doorheen te praten.

[figure not shown]

6. Ik ben er zeker van dat ik iets kan afmaken binnen de tijd die ik gepland had.

[figure not shown]

7. Ik ben er zeker van dat ik geconcentreerd kan blijven om taken te doen binnen mijn geplande tijd.

[figure not shown]

8. Ik ben er zeker van dat ik mijn taken doe binnen de tijd die ik gepland ervoor gepland heb.

[figure not shown]

9. Ik ben er zeker van dat ik een nieuw plan kan proberen te maken, ook al is mijn eerste plan mislukt.

[figure not shown]

10. Ik ben er zeker van dat ik kan oefenen om beter te worden in het op tijd afmaken van taken.

[figure not shown]

11. Ik ben er zeker van dat ik rustig kan blijven en kan doorzetten zelfs als mijn plan niet werkt.

[figure not shown]

12. Ik ben er zeker van dat ik iets kan bereiken/afmaken zonder afgeleid of verveeld te raken.

[figure not shown]

13. Ik ben er zeker van dat ik nieuwe manieren kan leren om taken op tijd af te krijgen.

[figure not shown]

14. Ik ben er zeker van dat ik goede plannen kan blijven bedenken, zelfs als mijn plannen niet werken.

[figure not shown]

## 1. Questionnaires teachers, version 01

Het is de bedoeling dat u bij onderstaande beschrijvingen (middels nooit, soms, vaak) aangeeft in welke mate deze van toepassing is op uw leerling zoals hij/zij nu is of in de afgelopen twee weken is geweest.

|                                                                                                                                | Nooit                 | Soms                  | Vaak                  |
|--------------------------------------------------------------------------------------------------------------------------------|-----------------------|-----------------------|-----------------------|
| 1. Onthoudt alleen het eerste of het laatste als hij/zij drie dingen te doen krijgt                                            |  |  |  |
| 2. Kan zich maar kort concentreren                                                                                             |  |  |  |
| 3. Neemt huiswerk, opgaven, spulletjes etc. niet mee naar huis                                                                 |  |  |  |
| 4. Heeft goede ideeën, maar krijgt ze niet op papier                                                                           |  |  |  |
| 5. Heeft moeite zich te concentreren op karweitjes, schoolwerk etc                                                             |  |  |  |
| 6. Is snel afgeleid door geluid, activiteit, uitzicht etc.                                                                     |  |  |  |
| 7. Vergeet huiswerk in te leveren, ook als het af is (als de leerling nooit huiswerk krijgt, kruis hier het vakje "nooit" aan) |  |  |  |
| 8. Heeft moeite met karweitjes of taken die meer dan een stap vereisen                                                         |  |  |  |
| 9. Heeft hulp nodig van een volwassene om bij de les te blijven                                                                |  |  |  |
| 10. Raakt verstrikt in details en verliest het algemene overzicht                                                              |  |  |  |
| 11. Vergeet wat hij/zij aan het doen was                                                                                       |  |  |  |
| 12. Als hij/zij iets moet halen, vergeet hij/zij wat het ook alweer was                                                        |  |  |  |
| 13. Heeft goede ideeën, maar kan ze niet uitvoeren (geen doorzettingsvermogen)                                                 |  |  |  |
| 14. Raakt overweldigd door grote opgaven                                                                                       |  |  |  |
| 15. Heeft moeite om dingen af te maken (karweitjes, huiswerk)                                                                  |  |  |  |
| 16. Onderschat de tijd die nodig is om taken af te maken                                                                       |  |  |  |
| 17. Begint pas op het laatste moment aan opdrachten of karweitjes                                                              |  |  |  |
| 18. Denkt niet vooruit bij huiswerkopdrachten (als de leerling nooit huiswerk krijgt, kruis hier het vakje "nooit" aan)        |  |  |  |
| 19. Geschreven werk ziet er slordig uit                                                                                        |  |  |  |
| 20. Heeft moeite om dingen te onthouden, zelfs voor een paar minuten                                                           |  |  |  |
| 21. Beheerst zijn/haar woede in conflictsituaties met leeftijdsgenoten                                                         |  |  |  |
| 22. Stelt zich uit zichzelf voor aan onbekenden.                                                                               |  |  |  |

|                                                                                                   | Nooit                 | Soms                  | Vaak                  |
|---------------------------------------------------------------------------------------------------|-----------------------|-----------------------|-----------------------|
| 23. Stelt op een goede manier vragen bij regels die onrechtvaardig zouden kunnen zijn.            |  |  |  |
| 24. Past in conflictsituaties eigen mening aan om tot overeenstemming te komen.                   |  |  |  |
| 25. Reageert op een goede manier op druk van leeftijdsgenoten.                                    |  |  |  |
| 26. Zegt op het juiste moment positieve dingen over zichzelf.                                     |  |  |  |
| 27. Nodigt anderen uit om aan activiteiten deel te nemen.                                         |  |  |  |
| 28. Gaat op een goede manier met vrije momenten om.                                               |  |  |  |
| 29. Voltooit opdrachten binnen de gegeven tijd.                                                   |  |  |  |
| 30. Maakt gemakkelijk vrienden.                                                                   |  |  |  |
| 31. Reageert op een goede manier op pesten door leeftijdsgenoten.                                 |  |  |  |
| 32. Beheerst woede in conflictsituaties met volwassenen.                                          |  |  |  |
| 33. Gaat goed met kritiek om.                                                                     |  |  |  |
| 34. Begint uit zichzelf gesprekken met leeftijdsgenoten.                                          |  |  |  |
| 35. Maakt goed gebruik van de tijd terwijl hij/zij op hulp moet wachten.                          |  |  |  |
| 36. Maakt zijn/haar schoolwerk netjes.                                                            |  |  |  |
| 37. Vertelt u op een goede manier wanneer hij/zij vindt dat u hem/haar oneerlijk heeft behandeld. |  |  |  |
| 38. Accepteert voorstellen van leeftijdsgenoten om samen dingen te doen.                          |  |  |  |
| 39. Geeft complimenten aan leeftijdsgenoten.                                                      |  |  |  |
| 40. Volgt uw instructies op.                                                                      |  |  |  |
| 41. Ruimt werkmateriaal of spullen van school op.                                                 |  |  |  |
| 42. Werkt uit zichzelf samen met andere kinderen.                                                 |  |  |  |
| 43. Biedt uit zichzelf aan om andere kinderen te helpen bij schooltaken.                          |  |  |  |
| 44. Sluit zich aan bij een activiteit of een groepje zonder daartoe aangezet te worden.           |  |  |  |
| 45. Reageert op een goede manier bij duwen of slaan door andere kinderen.                         |  |  |  |
| 46. Negeert storend gedrag van andere kinderen tijdens werken in de klas.                         |  |  |  |
| 47. Houdt uit zichzelf zijn/haar tafel schoon en netjes.                                          |  |  |  |

|                                                                             | Nooit                 | Soms                  | Vaak                  |
|-----------------------------------------------------------------------------|-----------------------|-----------------------|-----------------------|
| 48. Luistert aandachtig wanneer u aanwijzingen geeft.                       |  |  |  |
| 49. Maakt gemakkelijk de overgang van de ene klasactiviteit naar de andere. |  |  |  |
| 50. Kan goed overweg met mensen die anders zijn.                            |  |  |  |

Het is de bedoeling dat u bij onderstaande beschrijvingen (middels een cijfer van 1 tot en met 10) aangeeft in welke mate deze van toepassing is op uw leerling zoals hij/zij nu is of in de afgelopen twee weken is geweest.

|                                                                                                             | Helemaal
niet waar |                       |                       |                       |                       |                       |                       | Helemaal
waar      |                       |                       |
|-------------------------------------------------------------------------------------------------------------|-----------------------|-----------------------|-----------------------|-----------------------|-----------------------|-----------------------|-----------------------|-----------------------|-----------------------|-----------------------|
|                                                                                                             | 1                     | 2                     | 3                     | 4                     | 5                     | 6                     | 7                     | 8                     | 9                     | 10                    |
| 1. Mijn leerling kan een korte taak afmaken, binnen de door u bepaalde tijd                                 |  |  |  |  |  |  |  |  |  |  |
| 2. Mijn leerling kan bedenken hoeveel tijd nodig is om een klusje voor een deadline af te maken             |  |  |  |  |  |  |  |  |  |  |
| 3. Mijn leerling kan zonder hulp binnen een bepaalde tijd het ochtendritueel doorlopen                      |  |  |  |  |  |  |  |  |  |  |
| 4. Mijn leerling kan zonder hulp binnen een redelijke tijd dagelijkse activiteiten uitvoeren                |  |  |  |  |  |  |  |  |  |  |
| 5. Mijn leerling kan zijn/haar huiswerkplanning aanpassen ten behoeve van andere activiteiten               |  |  |  |  |  |  |  |  |  |  |
| 6. Mijn leerling kan op tijd met een lange termijnproject beginnen. Zodat de kans op tijdnood kleiner wordt |  |  |  |  |  |  |  |  |  |  |
| 7. Mijn leerling heeft huiswerk meestal af                                                                  |  |  |  |  |  |  |  |  |  |  |
| 8. Mijn leerling neemt goede beslissingen over prioriteiten als de tijd beperkt is                          |  |  |  |  |  |  |  |  |  |  |
| 9. Mijn leerling kan een lange termijnproject over verschillende dagen uitsmeren                            |  |  |  |  |  |  |  |  |  |  |
| 10. Mijn leerling raffelt op het laatste moment klusjes en/of taken af                                      |  |  |  |  |  |  |  |  |  |  |
| 11. Mijn leerling kijkt uit zichzelf regelmatig op de klok (of zijn/haar horloge)                           |  |  |  |  |  |  |  |  |  |  |

### ***J. Game Experience Self constructed Questionnaire, version 01***

Onderstaande vragen hebben betrekking op het computergebruik van uw kind. Er wordt aan u gevraagd uit één alternatief te kiezen en het bijbehorende antwoord aan te kruisen.

Vraag 1. Hoe vaak zit uw kind thuis achter de computer?

- ☐ nooit, want ik heb thuis geen computer
- ☐ nooit, maar ik heb thuis wel een computer
- ☐ ongeveer één keer per maand
- ☐ ongeveer één keer per week
- ☐ ongeveer twee tot drie keer per week
- ☐ (bijna) ieder dag

Vraag 2. Heeft u thuis een spelcomputer (o.a. xbox360, Nintendo, playstation)?

- ☐ nee
- ☐ ja

Vraag 3. Hoeveel uur per week speelt uw kind een spel op de computer/spelcomputer?

- ☐ 0 uur
- ☐ 1-5 uur
- ☐ 5-10 uur
- ☐ meer dan 10 uur

Vraag 4. Hoe ervaren vindt u uw kind op het gebied van computergebruik?

- ☐ beginner
- ☐ amateur
- ☐ ervaren
- ☐ expert

### K. Satisfaction Parents, Self constructed questionnaire, version 02

Onderstaande vragen hebben betrekking op uw ervaringen met de verschillende aspecten van het computerspel. Het is de bedoeling dat u onderstaande vragen beantwoordt middels een cijfer van 1 tot en met 10. Bij enkele andere vragen kunt u het antwoord achter de vraag schrijven.

|                                                                                                          | Helemaal
niet      |                       |                       |                       |                       |                       |                       |                       | Helemaal
wel       |                       |
|----------------------------------------------------------------------------------------------------------|-----------------------|-----------------------|-----------------------|-----------------------|-----------------------|-----------------------|-----------------------|-----------------------|-----------------------|-----------------------|
|                                                                                                          | 1                     | 2                     | 3                     | 4                     | 5                     | 6                     | 7                     | 8                     | 9                     | 10                    |
| 1. Hoe belastend was het spelen van het computerspel voor uw kind?                                       |  |  |  |  |  |  |  |  |  |  |
|                                                                                                          | Helemaal
niet      |                       |                       |                       |                       |                       |                       |                       | Helemaal
wel       |                       |
|                                                                                                          | 1                     | 2                     | 3                     | 4                     | 5                     | 6                     | 7                     | 8                     | 9                     | 10                    |
| 2. Hoe belastend was het spelen van het computerspel voor het gezin (u en eventuele andere gezinsleden)? |  |  |  |  |  |  |  |  |  |  |
|                                                                                                          | Te kort               |                       |                       |                       |                       |                       |                       |                       | Te lang               |                       |
|                                                                                                          | 1                     | 2                     | 3                     | 4                     | 5                     | 6                     | 7                     | 8                     | 9                     | 10                    |
| 3. Wat vindt u van het aantal minuten per dag dat uw kind het computerspel mocht spelen?                 |  |  |  |  |  |  |  |  |  |  |
|                                                                                                          | Te weinig             |                       |                       |                       |                       |                       |                       |                       | Te veel               |                       |
|                                                                                                          | 1                     | 2                     | 3                     | 4                     | 5                     | 6                     | 7                     | 8                     | 9                     | 10                    |
| 4. Wat vindt u van het aantal keer dat uw kind het computerspel mocht spelen?                            |  |  |  |  |  |  |  |  |  |  |
|                                                                                                          | Helemaal
niet      |                       |                       |                       |                       |                       |                       |                       | Helemaal
wel       |                       |
|                                                                                                          | 1                     | 2                     | 3                     | 4                     | 5                     | 6                     | 7                     | 8                     | 9                     | 10                    |
| 5. Hoe gemotiveerd was uw kind om het computerspel game te spelen?                                       |  |  |  |  |  |  |  |  |  |  |
|                                                                                                          | Te weinig             |                       |                       |                       |                       |                       |                       |                       | Te veel               |                       |
|                                                                                                          | 1                     | 2                     | 3                     | 4                     | 5                     | 6                     | 7                     | 8                     | 9                     | 10                    |
| 6. Hoeveel moeite kostte het u om uw kind te motiveren om het computerspel te blijven spelen?            |  |  |  |  |  |  |  |  |  |  |

|                                                                                                                                                                                              | 1                     | 2                     | 3                     | 4                     | 5                     | 6                     | 7                     | 8                     | 9                     | 10                    |
|----------------------------------------------------------------------------------------------------------------------------------------------------------------------------------------------|-----------------------|-----------------------|-----------------------|-----------------------|-----------------------|-----------------------|-----------------------|-----------------------|-----------------------|-----------------------|
| 7. Op school worden altijd rapportcijfers gegeven, een 10 is zeer goed, een 6 is voldoende en een 1 is zeer slecht. Welk cijfer zou u geven aan het computerspel dat uw kind gespeeld heeft? |  |  |  |  |  |  |  |  |  |  |

1 is zeer slecht. Welk cijfer zou u geven aan het computerspel dat uw kind gespeeld heeft?

8. Denkt u dat uw kind iets geleerd heeft van het computerspel?

☐ Ja, omdat.....

☐ Nee, omdat.....

☐ Ik weet het niet

Indien ja, beschrijf

.....

.....

.....

9. Heeft u nog op- en/of aanmerkingen met betrekking tot bovengenoemde vragen?

.....

.....

.....

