### **2.3 Secondary objectives**

The secondary objective of this research is to examine the effects of Healseeker on working memory and self efficacy. In addition, it is examined whether intervention effects vary as a function of gender, age, ethnicity, SES, intelligence level, comorbidity, game experience, severity of psychopathology and satisfaction. The distribution of these baseline characteristics should be taken into account when answering this additional question.

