#### **Baseline measurement of game experience and use**

**Instrument: Self-constructed questionnaire** filled out by parents/legal guardians (**Attachment.J**)

This questionnaire examines the experience level of children concerning gaming and computer use.

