## 8. STATISTICAL ANALYSES

The modified ITT analysis set will include all randomized subjects who have both a baseline and at least one post-baseline efficacy assessment. Hochberg procedure (Biometrika, 1988) will be used to control the experiment-wise alpha level at 0.05 for the multiple primary endpoint analyses. All tests will be two-sided.

For all outcome measures descriptive statistics (mean, SD, median and range) as well as their changes from T0 (Baseline) will be calculated by treatment group. Within-group comparisons of changes at T1 (Week 10) from T0 will be conducted in both groups.

To assess whether effects are maintained after stopping the game, within-group comparisons of changes at T2 (Week 20) versus T1 will be performed in the Immediate group. To assess effects of game after waiting period, within-group comparison of changes at T2 versus T1 will be conducted in the delayed group.

An analysis of covariance (ANCOVA) model that includes treatment, site and gender as factors and baseline as covariate, will be used for the primary outcome measures to estimate the difference between the two groups in changes from T0 at T1.

Exploratory analyses may be conducted as deemed appropriate to examine whether intervention effects vary as function of demographic and baseline characteristics (e.g. age, gaming experience), to explore correlations between different measures, to investigate potential mediating effects (e.g. working memory, self-efficacy).

All adverse events will be listed. Special attention will be given to those subjects who discontinued due to an adverse event.

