### **9.6 Benefits and risks assessment, group relatedness**

Both children and their parents/legal guardians will be well informed about the goals and used methods in this study, and of the advantages and disadvantages of joining, and brochures for parent and child have been made solely for this purpose. The risks of this

intervention are limited, especially since the study does in no way interfere with regular treatment or education of the children with ADHD. Thereby, the risk of game addiction is negligible. Game addiction occurs in situations of children playing games for more than 40 hours per week (Van Rooij, Schoenmakers, Meerkerk & Van de Mheen, 2009). The maximum game play time per day is set at 45 minutes for both HealSeeker, combined with 20 minutes in the social community (HealSeeker). Because of the limited available game time, the risk of addiction is minimal. In addition, most addictive games have a component of random rewards. This is not the case in HealSeeker in which only positive behaviour is rewarded. Finally, the prevalence rates of game addiction in children 13 till 16 years of age are very low and even lower in younger children. The risk of addiction is not very likely for the age group included in this study. The current study concerns a therapeutic intervention through a computer game. The goal of this training is to enhance time management, organisational skills, planning and social skills in children with ADHD through a computer game with built-in learning goals. The computer game can be played online and at home. The risks of participation can be considered negligible and the burden can be considered minimal. This study provides children with ADHD with the opportunity to join a non-medicinal intervention aimed at abating associated problems and elevating empowerment. Parents/legal guardians and the child can withdraw from the intervention at any moment, without questions or further consequences.

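### The weekly gaming-hours question in Attachment J has answer boxes that overlap at 5 hours and leave a gap between 0 and 1 hour, so some children can be classified inconsistently on an exploratory effect modifier

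*Protocol*

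**What the plan says.** Attachment J is a four-item parent questionnaire. Its instruction is to choose one alternative: "Er wordt aan u gevraagd uit één alternatief te kiezen en het bijbehorende antwoord aan te kruisen". Question 3 reads "Hoeveel uur per week speelt uw kind een spel op de computer/spelcomputer" and offers 0 hours, 1–5 hours, 5–10 hours and "meer dan 10 uur".

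The other items ask how often the child uses the home computer (question 1), whether there is a games console at home (question 2) and how experienced the parent rates the child in computer use (question 4). Section 6.1.4 states the purpose of the whole form: "This questionnaire examines the experience level of children concerning gaming and computer use". Section 3.5 says the game-experience questionnaire is taken only once, and Table 1 places it at T0 only.

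Section 2.3 says that "it is examined whether intervention effects vary as a function of gender, age, ethnicity, SES, intelligence level, comorbidity, game experience, severity of psychopathology and satisfaction". Section 8 is softer. Exploratory analyses may be done, as deemed appropriate, to see whether effects "vary as function of demographic and baseline characteristics (e.g. age, gaming experience".

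**The concern.** Answer boxes for a single-choice question should be mutually exclusive and should cover every possible answer. These do neither. The overlap falls on a round number that a parent could easily give. Two children who both play 5 hours a week can be recorded in different boxes, and a child who plays half an hour has no correct box.

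At stake is the quality of one baseline variable. In a trial of a computer game, prior gaming is a natural candidate for an effect modifier, and section 2.3 names it as one. Question 3 is the only item that measures how much the child plays. Because it is asked once, no later analysis rule can recover which box a 5-hour or half-hour child should have been in.

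**Working it through.** **Step 1. Map hours to the printed boxes**, reading both bounds as inclusive.

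| Hours per week | Boxes that fit |
|---|---|
| 0 | 0 |
| 0.5, 0.75 | none |
| 1, 3 | 1–5 |
| 5 | 1–5 and 5–10 |
| 7, 10 | 5–10 |
| 10.5, 12, 40 | more than 10 |

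There is one overlap (at 5) and one gap (above 0 and below 1). At 10 hours there is neither. This step needs no assumption.

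**Step 2. How many children could be ambiguous.** The protocol gives no distribution of gaming hours, so the share s is an assumption, taken as 2% to 15% of the 170 children in section 4.1:
- 0.02 × 170 = 3.4
- 0.15 × 170 = 25.5

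That is about 3 to 26 children.

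**Step 3. Effect on a two-group moderator analysis.** Assume an even split and that half of the ambiguous children land on the wrong side, so the misclassified fraction is m = s/2 = 1% to 7.5%. Assume also that this is symmetric and unrelated to treatment arm. An interaction is then multiplied by 1 − 2m:
- m = 0.01: 0.98, an attenuation of 2%
- m = 0.075: 0.85, an attenuation of 15%

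This leans to the pessimistic side. A single split is blurred by either the overlap or the gap, not both, and a 5-hour child lies on the boundary, not far into the wrong group.

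**Step 4. What this means for power.** Section 4.5 uses an SD of 16, a difference of 8 points and 78 children per group. Its own figure reproduces: 8 / (16 × √(2/78)) = 3.12, and Φ(3.12 − 1.96) = 87.7% (87.3% with the t distribution), against the stated 87%.

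For an interaction between arm and an even two-group split there are four cells of N/4, so SE = 16 × √(16/N). With N = 2 × 78 = 156, SE = 5.12. For an assumed interaction of 8 points:
- no misclassification: Φ(8/5.12 − 1.96) = 35%
- m = 0.01: Φ(7.84/5.12 − 1.96) = 33%
- m = 0.075: Φ(6.8/5.12 − 1.96) = 26%

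The analysis has low power even with perfect boxes. The wording fault makes it somewhat worse.

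**The case against.** The strongest reply is that this is a wording slip on one of four items, feeding an analysis that section 8 leaves optional. Game experience is not in the primary ANCOVA (section 8), the randomisation strata (section 6.2) or the eligibility criteria (sections 4.2 and 4.3). Parents' hours are rough estimates anyway, and a parent who answers in whole hours never meets the gap. All of this stands and it limits the importance of the point. It does not remove the overlap and the gap, which are visible on the form.

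Four stronger readings are tempting, and the protocol does not support them.

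- **The open top box is an error.** It is not. Every value above 10 fits it and it does not overlap the box below, so nobody is misclassified there. It only loses resolution among heavy players. The statement in section 9.6 that "Game addiction occurs in situations of children playing games for more than 40 hours per week" is an argument about addiction risk, and children addicted to gaming are excluded (section 4.3, criterion 2).
- **The boxes throw away a large part of the information.** If hours are assumed log-normal with median 3, 5 or 8 and log-SD 0.6 to 0.9, boxes cut at 5 and 10 and read without overlap keep about 50–80% of the variance of log hours. That is the price of coarse categories, and corrected boxes with the same cut points would pay it too. It does not measure the overlap or the gap.
- **Children are in fact misclassified.** Only those at exactly 5 hours or under 1 hour are ambiguous, and their number is unknown.
- **Question 3 is the moderator.** No section says so. Game experience could be scored from several items, and a scoring rule may stand in the statistical analysis plan, which is not shown.

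**Conclusion.** The point holds as a minor flaw in data collection. The overlap and the gap are certain. Their size is not: the 2–15% attenuation rests on an assumed 2–15% of ambiguous children, an even two-group split, half of those children falling on the wrong side, and errors unrelated to arm. The consequence is confined to the exploratory question of whether the effect varies with game experience, and to describing that characteristic at baseline. The estimate of the treatment effect on the three primary outcomes does not depend on it.

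**What to change.** Reword the options of question 3 so that each possible answer fits exactly one box, for example: 0; more than 0 to less than 5; 5 to 10; more than 10 hours per week. This changes the labels on one form and adds no time for parents. It has to be done before the questionnaire is used, because the answers are not collected again.

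A single numeric field for hours per week, with 0 and half hours allowed, is an optional alternative. It would also restore resolution among heavy players. Its small downside is that parents' figures are rough estimates. This is a preference and is not needed to remove the fault.
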